### Sample size

Participants recruited in Study II will be randomly assigned to one of the three groups of Study III (cf. Figure. 1). G*Power was used to calculate sample size considering Study III requirements for repeated measures analysis with two groups (considering that the RCT groups will be compared two at a time) and 4 assessment moments. Power analysis for medium effects (f = 0.25) – chosen based on previous ACT studies with adolescents (e.g., [27–30, 60, 80]) –, with a significance level of 0.05 and power of 0.95 requires a sample size of 25 per group. To account for the expected 17% dropout rate reported in a previous meta-analysis of ACT-based interventions [81], the research team intends to collect 4 additional participants per group. Accordingly, Study II will rely on two clinical groups (i.e., SAD and GAD,n ≥ 87) of at least 44 adolescents each, and a mentally healthy group of 29 adolescents (i.e., total n for Study II ≥ 116). For Study III, the clinical participants (i.e., n ≥ 87) will be then assigned to two intervention groups of 29 adolescents each, one for SAD and one for GAD participants, or to a control group of 29 adolescents, evenly distributed between adolescents presenting with SAD or GAD diagnoses.

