### Study design and randomization of participants

The two aims of this research will be accomplished through diverse study designs. To accomplish the first aim, cross-sectional data will be collected from adolescents within a community sample, two clinical groups (with SAD or GAD), and a mentally healthy sample. For the second aim, a Randomized Controlled Trial (RCT) with a parallel design, 3 groups (i.e., Control Group, SAD Intervention Group, and GAD Intervention Group) and 4 assessment moments will be conducted following the CONSORT (Consolidated Standards of Reporting Trials) guidelines [77]. Adolescents from each clinical group from Study II will be randomly allocated (computer-generated random allocation,2:1 allocation ratio) to one of the intervention groups or to the control group. The two clinical intervention groups will receive the same intervention and will be assessed at pre- and post-intervention, and at 3- and 6- month follow-up using a set of self-report measures (see measures section). Adolescents from the control group will be assessed with the same set of self-report measures at 2 different time points (12 weeks interval), mimicking the pre- and post-intervention assessment moments. Given the high stability of both SAD and GAD, we consider ethical obligations to be imperative in not depriving these adolescents of intervention during follow-up assessments. As such, they will be assessed with a clinical structured interview (Mini-Kid; [78]) after the second time point and referred to the school psychology services if the difficulties persist. A flowchart of the study design is presented in Fig. 1.

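### The sample size assumes four assessments in every pairwise comparison, but controls are assessed only twice, so the calculation does not support the stated 95% power for ACT versus control

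*Protocol article*

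**What the plan says.** The Sample size section describes the G*Power calculation as one for "repeated measures analysis with two groups (considering that the RCT groups will be compared two at a time) and 4 assessment moments". The inputs and result are "Power analysis for medium effects (f = 0.25", then "with a significance level of 0.05 and power of 0.95 requires a sample size of 25 per group". The section continues "To account for the expected 17% dropout rate", and says that "the research team intends to collect 4 additional participants per group", which makes 29 per group. It states neither the correlation among repeated measures nor a nonsphericity correction.

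The section on study design and randomization calls the trial one with "3 groups (i.e., Control Group, SAD Intervention Group, and GAD Intervention Group) and 4 assessment moments". It then separates the schedules. The two ACT groups "will be assessed at pre- and post-intervention, and at 3- and 6- month follow-up using a set of self-report measures". For the control group it says: "Adolescents from the control group will be assessed with the same set of self-report measures at 2 different time points (12 weeks interval", and explains that these two points stand in for pre- and post-intervention.

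The Aims section places the ACT-versus-control hypothesis at post-intervention and treats the 3- and 6-month data as a question of maintenance in the two ACT groups. The Data analysis section plans mixed ANOVAs with assessment moment within subjects and all three groups between subjects. It does not say that analyses including controls use two moments.

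**The concern.** Three pairwise comparisons are possible, and two of them involve controls: SAD-ACT versus control and GAD-ACT versus control. These carry the efficacy question. Both are two-group, two-assessment designs, because controls have nothing after the second assessment. The power statement rests on a four-assessment design that only SAD-ACT versus GAD-ACT has.

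In the formula behind this kind of calculation the noncentrality is proportional to the number of assessments. Carrying a four-assessment figure over to a two-assessment contrast therefore overstates power at the same f and rho. A reader would take the published 95% as applying to the efficacy comparisons, and would read a null result there with more confidence than the calculation justifies.

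**Working it through.** **Inputs from the article.** f = 0.25, alpha 0.05, target power 0.95, k = 2 groups per comparison, m = 4 assessments in the calculation, m = 2 assessments for controls, 25 per group (N = 50 per comparison), 29 per group after the dropout allowance (N = 58).

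**Not stated, so assumed and varied.** rho, the correlation among repeated measures, and eps, the nonsphericity correction. eps = 1 means sphericity; with m = 2 it has no effect.

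**Formula** (noncentral F, within-between interaction):
- lambda = f² × N × m × eps / (1 − rho)
- df1 = (k − 1)(m − 1) × eps
- df2 = (N − k)(m − 1) × eps

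**Step 1: reproduce the article's figure (m = 4).**
- rho 0.3, eps 1, N = 50: lambda = 0.0625 × 50 × 4 / 0.7 = 17.86, df 3 and 144, power 95.2%. N = 48 gives 94.4%. So 25 per group reproduces, and it does so for rho 0.30–0.32.
- rho 0.5, eps 1: N = 36, or 18 per group, already gives 95.2%. This does not reproduce 25.
- rho 0.5, eps 0.63–0.66: N = 50, or 25 per group. This reproduces too.

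Two different sets of unstated inputs therefore give 25 per group, and the article does not say which was used.

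**Step 2: the contrast that controls allow (m = 2, f = 0.25).** Example at rho 0.3, N = 50: lambda = 0.0625 × 50 × 2 / 0.7 = 8.93, df 1 and 48, power 83.3%.

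| rho | power, 25 per group | power, 29 per group | needed per group for 95% |
|---|---|---|---|
| 0.30 | 83.3% | 88.5% | 38 |
| 0.32 | 84.4% | 89.4% | 37 |
| 0.50 | 93.4% | 96.3% | 27 |
| 0.54 | 95.1% | 97.4% | 25 |
| 0.60 | 97.2% | 98.7% | 22 |
| 0.70 | 99.4% | 99.8% | 17 |

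The 95% target is reached from rho of about 0.54 with 25 per group, and from about 0.46 with 29.

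**Step 3: four against two at the same f and rho, with sphericity at m = 4.** With N = 50, power is 95.2% against 83.3% at rho 0.3, and 99.2% against 93.4% at rho 0.5. Halving m halves lambda (17.86 to 8.93; 25.0 to 12.5), and the loss of numerator degrees of freedom does not make up for it.

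**Step 4: what f = 0.25 means with two groups and two assessments.** It corresponds to interaction cell effects of ±0.25 SD, so the between-group difference in change is 4 × 0.25 = 1.0 SD. Check: for a difference in change d in SD units, the change-score test has noncentrality d²N / [8(1 − rho)]. With d = 1, N = 50 and rho 0.3 this is 50 / 5.6 = 8.93, the same as in step 2.

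**The case against.** The strongest reply is that the loss may be small or absent. The article gives no rho, and rho 0.3 with sphericity is a back-fit. The pair rho 0.5 with eps 0.63–0.66 fits equally well and puts two-assessment power at 93.4% with 25 per group, less than two points short. The Data analysis section also includes everyone randomized, so the planned analysis set is 29 per group, where rho 0.5 gives 96.3%. Power actually delivered depends on the true pre/post correlation, not on the one entered for planning. All of this stands. A reader might infer that the trial cannot reach 95% power for any comparison with control, or that 83% should be printed instead; the documents support neither. What the reply does not do is make a four-assessment calculation describe a two-assessment contrast.

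A reader might also infer that the trial is badly powered for a 0.5 SD difference in change and count that against the plan. The article states f = 0.25 and claims no 0.5 SD effect, so that would test a target it never set. The 1.0 SD equivalence matters only for interpreting f.

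Finally, a reader might infer that a four-moment ANOVA will drop all controls, or that last observation carried forward will fill in their 3- and 6-month scores. The article states neither. Its missing-data examples are refusals and unreachable participants, and the Aims section already points to a pre/post comparison with control. The narrower point that remains is that the Data analysis section does not limit analyses with controls to two moments.

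**Conclusion.** The point holds as a wrong input to a stated figure. The 95% power at 25 per group comes from a four-assessment design that neither ACT-versus-control comparison has, so the calculation does not support it there.

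The size is a range, because rho and eps are not stated. Over rho 0.3 to 0.7, two-assessment power runs from 83% to over 99% with 25 per group, and from 88.5% to 99.8% with 29. The shortfall is about 11 to 12 points with 25 per group if rho was 0.30–0.32 under sphericity. It is under 2 points at rho 0.5 and gone from about 0.54.

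These figures hold f at 0.25 for both designs. That is itself an assumption, since an effect size for a four-moment interaction need not carry over to a two-moment one.

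**What to change.** In the Sample size section, state the rho and eps entered in G*Power. Recompute power for the two-assessment ACT-versus-control contrast, at 25 and at 29 per group, and report it over a plausible range of rho rather than as one figure. Add that f = 0.25 in this 2 × 2 interaction corresponds to a 1.0 SD between-group difference in change. Keep the four-assessment calculation, if wanted, for SAD-ACT versus GAD-ACT and label it so.

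In the design and Data analysis sections, state that efficacy is tested on pre/post data in all arms. State that the four-moment analysis is restricted to the ACT arms and reported as uncontrolled maintenance. Add that last observation carried forward is not applied to control visits that were never scheduled.

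The cost is one recalculation and some wording, with a possibly less favourable stated power. No extra participants are required.

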### Data analysis

IBM SPSS Statistics 25 will be used to conduct descriptive analysis. In study I, network analysis will be performed and visualized using R (Version 4.1.3). Network nodes will represent the scores for each PI/PF subscales and total scores for anxiety and flourishing measures. Edges will represent the weight of the correlations between the individual nodes. Centrality metrics (e.g., degree of centrality) will also be computed to investigate how important and influential each node is in the network. In study II, Mplus will be used to investigate the adjustment of a path analysis linking PI/PF processes to anxiety and flourishing, based on overall, comparative and residual based fit-indices. The moderator effect of groups (clinical SAD, clinical GAD and healthy adolescents) in those pathways will be estimated, testing for equality of pathways and means. In Study III, the IBM SPSS Statistics 25 will be used to explore treatment effects using Mixed ANOVAs and considering assessment moments as the within-subject and groups (SAD and GAD receiving intervention and Control Groups) as the between-subject effect; interaction effects will also be considered. Additionally, Mplus will be used to examine mechanisms of change after the intervention by performing two-wave latent change score models. These models allow to explore not only if significant changes emerged across assessment moments, but also to investigate the impact of changes in PI/PF constructs on changes in anxiety or flourishing. All Study III analyses will be carried out according to an intention-to-treat principle as suggested by the CONSORT guidelines [77]. Therefore, all participants randomized will be included in the statistical analyses and analyzed according to the group they were assigned regardless of having received/completed or not the intended intervention. Efforts will be made to obtain outcome data for all participants, even if they do not complete the intervention. If data is missing (e.g., participant refused to provide data, participant was unreachable, etc.) the last observation carried forward method will be employed.

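### The claimed 0.95 power for medium effects is misstated: on the interaction scale that best reproduces 25 per group, f = 0.25 is a group difference in change of at least 1.0 SD

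*Protocol article*

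**What the plan says.** All references are to the Method of the protocol article.

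- **Sample size.** "G*Power was used to calculate sample size" for "repeated measures analysis with two groups (considering that the RCT groups will be compared two at a time) and 4 assessment moments". The effect is described with the words "Power analysis for medium effects (f = 0.25" and said to be "chosen based on previous ACT studies with adolescents". The result is stated as "with a significance level of 0.05 and power of 0.95 requires a sample size of 25 per group". Four participants per group are then added for dropout, giving 29.
- **Data analysis.** Study III will "explore treatment effects using Mixed ANOVAs and considering assessment moments as the within-subject" factor, with the three groups as the between-subject factor; "interaction effects will also be considered". The section does not say which term carries the efficacy claim.
- **Aims and Study design.** Improvement after the intervention is expected relative to control, and similar effects are expected in the social anxiety (SAD) and generalised anxiety (GAD) groups. The intervention groups are assessed four times. Controls are assessed twice, 12 weeks apart.

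The article does not state the F test, the correlation among repeated measures or the sphericity correction used in the calculation. It never converts f into a difference on an outcome scale.

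**The concern.** For two groups compared on one score, f is half the standardised difference. So f = 0.25 is d = 0.5, which is what most readers understand by a medium effect. In a repeated-measures routine the same f can mean something else, depending on which term is tested. If the sample size rests on the group-by-time interaction, 25 per group has high power only for a much larger difference than the label suggests.

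What is at stake is how a null result is read. A non-significant comparison of ACT with control, presented as having 95% power for medium effects, would look like evidence against a half-SD benefit. A non-significant SAD versus GAD comparison would look like support for the expected equivalence. Neither reading is safe if a 0.5 SD difference would often be missed.

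**Working it through.** **Inputs from the article:** k = 2 groups, m = 4 assessments, f = 0.25, alpha 0.05, power 0.95, 25 per group (N = 50 per two-group comparison).

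**Assumptions, because the article is silent:** correlation rho of 0.3, 0.5 or 0.7, equal at all pairs of assessments; equal SDs; no sphericity correction; no difference at baseline.

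**Step 1. Which calculation gives 25 per group?**

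*Group-by-time interaction:* lambda = f² × N × m / (1 − rho), with df = (k − 1)(m − 1) and (N − k)(m − 1).

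At rho = 0.3: lambda = 0.0625 × 50 × 4 / 0.7 = 17.86, df = 3 and 144, power = 0.952. This is the smallest balanced N reaching 0.95, so the stated figure is reproduced.

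*Between-group effect:* lambda = f² × N × m / (1 + (m − 1)rho), with df = 1 and N − 2.

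| rho | Total N, interaction | Total N, between-group | Between-group power at N = 50 |
|---|---|---|---|
| 0 | 72 | 54 | 93% |
| 0.3 | 50 | 102 | 71% |
| 0.5 | 36 | 132 | 59% |
| 0.7 | 24 | 164 | 50% |

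G*Power's SPSS and Cohen effect-size options need 96 and 94. The time main effect gives the same N as the interaction but tests no difference between groups. The interaction also reaches 50 at rho = 0.5 with a sphericity epsilon of about 0.63 to 0.66.

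**Step 2. What f = 0.25 means for the interaction.** With two equal groups, f is half the SD over time of the group difference, in within-cell SD units. Let D be the largest difference reached:

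- Two waves, pattern (0, D): f = D/4, so f = 0.25 gives D = 1.0 SD.
- Four waves, sustained, (0, D, D, D): f = 0.2165D, so D = 1.15 SD.
- Four waves, linear, (0, D/3, 2D/3, D): f = 0.1863D, so D = 1.34 SD.
- Any four-wave pattern: the SD of four values cannot exceed half their range, so f ≤ range/4 and the difference must move by at least 1.0 SD.

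These conversions do not depend on rho.

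**Step 3. Power for D = 0.5 SD at N = 50.** The interaction f is 0.5/4 = 0.125 with two waves and 0.2165 × 0.5 = 0.108 for a sustained four-wave effect.

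| Pattern | rho 0.3 | rho 0.5 | rho 0.7 |
|---|---|---|---|
| Two waves | 31% | 41% | 61% |
| Four waves, sustained | 30% | 41% | 63% |
| Four waves, most favourable pattern | 39% | 52% | 77% |

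Simulation of the sustained four-wave case gave 30%, 40% and 63%. With all 29 per group retained (N = 58), the two-wave figures are 35%, 46% and 68%.

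**Step 4. Difference detectable with 95% power at N = 50.**

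- *ACT versus control, two waves:* lambda = (D²/16) × 50 × 2 / (1 − rho) = 6.25D²/(1 − rho). With df 1 and 48, 95% power needs lambda of about 13.5, so D is about √(2.17(1 − rho)): 1.2 SD at rho 0.3, 1.0 SD at 0.5, 0.8 SD at 0.7. The plan's own f = 0.25 (1.0 SD) has 83% power at rho 0.3 and 93% at rho 0.5.
- *SAD versus GAD, four waves, sustained:* lambda = 0.2165² × D² × 200 / (1 − rho). At rho 0.3, 95% power is reached at D of about 1.15 SD.

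**The case against.** **The routine is inferred.** The article names neither the test nor the correlation, and a condensed article may leave both to the full protocol. A reader might infer that the sponsor demonstrably entered a between-group benchmark into an interaction formula. The article does not show that: it never calls f = 0.25 a between-group value or equates it with 0.5 SD, and other settings also reach N = 50. What remains is that, of the tests of a treatment difference, the interaction fits the stated inputs best. If the between-group test was meant, 25 per group falls short of 95% at any non-negative correlation.

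**The effect size is attributed to earlier adolescent ACT studies.** If those reported interaction effects of about 0.25 on this scale, the input could be right. They cannot be checked here, so no error in choosing the input is shown. The medium label would still mislead, because the value would stand for 1.0 SD or more.

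**Nothing is miscalculated.** Correct. The stated figure reproduces at power 0.952, so a reader who concludes that the arithmetic is wrong goes too far. The fault lies in what the power is said to be for.

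**The shortfall depends on an unknown correlation.** Also correct. A reader might take the best entry in the table, 77%, as proof that at least 18 points are always lost. That bound fails above rho 0.7: at rho 0.8 the most favourable four-wave pattern has 92% power, and the sustained one 82%. Two waves, which is all a comparison with control has, gives 78% there.

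**A baseline-adjusted analysis would do better.** Yes. For a two-wave comparison with residual SD √(1 − rho²), power at 0.5 SD is 46%, 53% and 70% at rho 0.3, 0.5 and 0.7. That is not the analysis planned, and it is still well below 95%.

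**Conclusion.** The point holds as a misstated power claim. No plausible reading of the stated inputs gives 95% power for a medium group difference. Under the interaction routine, f = 0.25 is a differential change of at least 1.0 SD, twice the conventional medium value. For 0.5 SD, the two-wave comparison with control has roughly 30% to 60% power over correlations 0.3 to 0.7, and the sustained four-wave SAD versus GAD comparison is much the same.

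The scale conversion is algebra and holds whatever the correlation. The power figures rest on equal SDs, equal correlations, no baseline difference and the assumed range of rho; they improve at higher correlations. That the interaction routine was used, with rho about 0.3, is the best-fitting inference and not a stated fact.

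**What to change.** Keep the sample size and revise the power statement in the Sample size section:

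1. Name the F test, the assumed correlation and any sphericity correction.
2. Delete the description of f = 0.25 as a medium effect.
3. State the difference detectable with 95% power separately for each contrast. For SAD versus GAD (four waves, rho 0.3) it is about 1.15 SD if sustained. For ACT versus control (two waves) it is about 1.2, 1.0 and 0.8 SD at rho 0.3, 0.5 and 0.7. A single statement of 95% power at f = 0.25 should not cover both contrasts, since the comparison with control has 83% there at rho 0.3.
4. Add the power at 0.5 SD across the correlation range.
5. State that a non-significant contrast does not exclude a 0.5 SD effect, including between SAD and GAD.

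The cost is one paragraph of text. No participants, assessments or analyses change, but the stated power becomes less favourable.

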
This study presents some foreseen limitations that are, nevertheless, necessary for its viability. Firstly, it focuses solely on SAD and GAD, disregarding other ADs that also present significant prevalence rates and impairments during adolescence. Additionally, the control group will not receive intervention within this project. To ensure these adolescents receive appropriate care, they will be assessed after completing the control condition and referred to school psychology services if difficulties persist. They will also be explicitly informed about the possibility of discontinuing their participation in the study to seek treatment, without any consequences. It is also important to note that the control group may not be entirely comparable to either of the intervention groups, which could lead to inherent disparities and the introduction of potential confounding variables. Based on ACT transdiagnostic premises, we believe that these differences will not significantly influence our findings. Nevertheless, the authors have devised a contingency plan to address this potential limitation, if necessary (i.e., gathering two independent control groups: one consisting solely of adolescents with SAD and another comprising only adolescents with GAD). We also acknowledge that by only using self-report measures, data collection may be susceptible to the effects of social desirability, and only a limited comprehension of the psychological constructs assessed is provided. Moreover, we anticipate dropouts to be a significant challenge in this study. To prevent its impact, the research team plans to recruit more participants than the minimum needed for each condition. This approach will allow us to account for potential attrition and ensure that sample size remains adequate throughout the study, maintaining statistical power. Efforts will be made to engage and motivate participants throughout the duration of the study to maximize retention rates (e.g., by sending thank you messages after each assessment moment). Lastly, we acknowledge that by not considering a group with comorbid GAD and SAD, we cannot fully elucidate the applicability of transdiagnostic principles to adolescents. Future research should consider comorbidity and/or cascading effects of mental health difficulties as relevant outcomes to better address the complex issues related to ACT as applied to adolescent mental health.

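### Four extra participants per group do not cover the expected 17% dropout: 29 per group leaves about 24 completers, one short of the required 25

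*Protocol article*

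**What the plan says.** All the figures are in the Sample size section of the protocol article. The power calculation, for two groups compared at four assessments, "requires a sample size of 25 per group". The next sentence opens "To account for the expected 17% dropout rate reported in a previous meta-analysis" and concludes that "the research team intends to collect 4 additional participants per group". The randomised groups then follow: clinical participants are "assigned to two intervention groups of 29 adolescents each", "or to a control group of 29 adolescents", which makes 87 in all. The clinical total is given as a minimum (n ≥ 87), while the three group sizes are given as plain 29s.

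The limitations part of the Discussion names dropout as a significant challenge and says that recruiting above the minimum will "account for potential attrition and ensure that sample size remains adequate throughout the study, maintaining statistical power".

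The Data analysis section states that all randomised participants will be analysed as assigned, with last observation carried forward (LOCF) where data are missing.

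**The concern.** Dropout is lost from the people recruited, so the recruitment target is the required number divided by the proportion retained. The allowance of 4 looks instead like 17% of the required 25 (4.25, taken as 4). The article does not show this step, so that is an inference, but no reading of the stated figures makes 4 extra enough for a 17% loss.

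At stake is whether the sample-size justification supports what the Discussion says about it. At the dropout rate the authors themselves expect, the groups would on average end below the number that the power calculation calls for. The same 29 fixes the trial total of 87.

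**Working it through.** **Inputs, all from the Sample size section:** required n = 25 per group; expected dropout d = 0.17; allowance = 4 per group; three randomised groups; f = 0.25, α = 0.05, target power 0.95, two groups, four assessments. The within-person correlation ρ and any sphericity correction are not given.

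**Reproducing the stated 29.** 25 + 4 = 29, and 3 × 29 = 87. The likely route is 25 × 0.17 = 4.25, rounded down to 4 (equivalently 25 × 1.17 = 29.25, rounded down).

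**What 29 retains.** Expected completers = 29 × (1 − 0.17) = 24.07 per group. Over the three groups, 87 × 0.83 = 72.2 against 3 × 25 = 75.

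**The dropout that 29 can absorb.** (29 − 25)/29 = 4/29 = 13.8%.

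**What 17% would need.** 25/(1 − 0.17) = 30.12, so 31 per group, or 93 randomised. Check: 30 × 0.83 = 24.9, just short; 31 × 0.83 = 25.73.

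**Chance of keeping 25.** If dropouts are independent with probability 0.17, a group of 29 keeps at least 25 with probability 0.44. For 30 it is 0.60 and for 31 it is 0.73.

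**Effect on power.** I used the noncentral F test of the group-by-time interaction with k = 2 groups, m = 4 assessments, total N, and sphericity assumed:

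- noncentrality λ = f²·N·m/(1 − ρ)
- degrees of freedom (k − 1)(m − 1) = 3 and (N − k)(m − 1)

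Because ρ is not stated, it has to be assumed. Values from 0.30 to 0.32 return the protocol's 25 per group at 95% power; ρ = 0.5 would return 18 per group (N = 36).

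| Assumed ρ | 25 per group (N = 50) | 24 per group (N = 48) | Loss |
|---|---|---|---|
| 0.3 | λ = 17.86, power 95.2% | λ = 17.14, power 94.4% | 0.8 points |
| 0.5 | λ = 25.0, power 99.2% | λ = 24.0, power 98.9% | 0.3 points |

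The dropout arithmetic does not depend on ρ or on how the 25 was obtained. Only the power figures do.

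**The case against.** The strongest reply is that the analysed number is not 24. The Data analysis section keeps every randomised participant in the analysis and fills gaps by LOCF, so the mixed ANOVAs would formally run on 29 per group. This stands as a correction to how 24 should be read: it is the expected number of completers. It does not rescue the allowance. The four extra were added specifically for dropout, so the article itself treats dropouts as lost from the 25, and a carried-forward value does not hold the information of an observed one.

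A second reply is that 87 is a minimum. That is true, but a minimum that falls short at the expected dropout rate is set too low for its stated purpose.

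Third, the Discussion speaks of attrition and power in general terms and names neither 17% nor 95%. This is fair. Its sentence is unsupported at the expected rate rather than a precise numerical claim that fails.

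Stronger readings are tempting but do not hold:

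- **Power falls well below target.** A reader might compute a two-assessment comparison with controls, who are measured only twice, and get 81.8% at 24 per group with ρ = 0.3. With no shortfall at all, at 25 per group, the same calculation already gives 83.3%. Only 1.5 points come from the dropout allowance; the rest comes from the number of assessments, which is a separate matter.
- **Power certainly drops below 95%.** This follows only if ρ is about 0.3, a value the article does not state. At ρ = 0.5 power stays near 99%.
- **The Study II total of 116 is wrong throughout.** Its 29 healthy adolescents are assessed cross-sectionally and have no follow-up to drop out of, so the correction does not reach them.

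**Conclusion.** The point holds, and it is small. On the article's own figures, 4 extra per group covers dropout up to 13.8%, not the expected 17%. About 24 completers per group are expected against 25 required, and full cover would take 31 per group. The shortfall is about one completer per group, costing 0.8 percentage points of four-assessment power if ρ = 0.3 and 0.3 points if ρ = 0.5.

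The arithmetic rests only on the stated 25, 17% and 4. The power figures rest on an assumed ρ, on sphericity, and on counting completers only. This is an error in a stated justification that should be corrected. It does not undermine the design.

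**What to change.** **Preferred.** In the Sample size section, state that 29 per group retains 25 completers at up to 13.8% dropout and about 24 at the expected 17%. If a power figure is attached, state the correlation it assumes. Qualify the Discussion's sentence on maintaining power in the same way, and make clear that these are completers while the intention-to-treat analysis includes all 29. The cost is one sentence plus that qualification, with no change to design or recruitment.

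**Alternative, if 17% is to be fully covered.** Set 31 per randomised group, 3 × 31 = 93 in place of 87, which is 6 more participants. Each clinical group in Study II would then need 31 + 31/2 = 46.5, so at least 47 instead of 44. The healthy group stays at 29, and the Study II minimum becomes 93 + 29 = 122 in place of 116.
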